## Abstract

**Background:**

Unreasonable use of antibiotics and probiotics can alter the gut ecology, leading to antibiotic resistance and suboptimal health outcomes during early life. Our study aims are to clarify the association among antibiotic and probiotic exposure in early life, the microecology of the gut microbiota, and the development of antibiotic resistance; to investigate the long-term impact of antibiotics and probiotics on the health outcomes of infants and young children; and to provide a theoretical basis for the rational use of antibiotics and probiotics from a life course perspective.

**Methods:**

The study is a prospective, longitudinal birth cohort study conducted in Shaanxi Province, China from 2018 to 2024. A total of 3,000 eligible mother–child pairs will be enrolled from rural, suburban, and urban areas. The recruitment of the participants begins at pregnancy, and the newborns will be followed up for 2 years at successive timepoints: within 3 days after birth, 42 days after birth, and at 3, 6, 12, 18, and 24 months of age. Sociodemographic data, environmental exposures, dietary patterns, psychological conditions, and medical and drug histories are collected. Cognitive and behavioural development among infants and young children and questionnaires on antibiotic knowledge and behaviour among caregivers will be collected at 12 and 24 months of age. The faecal samples are collected and analysed by 16S rRNA high-throughput sequencing and quantitative PCR (qPCR) for antibiotic resistance genes.

**Discussion:**

The findings will inform antibiotic and probiotic use for pregnant women and infants and contribute to establishing rational use strategies of antibiotics and probiotics for paediatricians, health practitioners, and drug administration policy-makers.

**Trial registration:**

The study was registered on the Chinese Clinical Trial Registry (ChiCTR) platform, http://www.chictr.org.cn (Record ID: ChiCTR2100047531, June 20, 2021).

## Background

The developmental origins of health and disease (DOHaD) concept highlights the importance of the first 1000 days (from conception to one’s second birthday), which is also a critical period for the establishment, gradual diversification, and stability of the gut microbiota. The early life stages are characterized by microbial immobilization and gut microbiota maturation in vivo, and their composition has lifespan implications on subsequent health outcomes [1]. Increasing evidence from epidemiological studies suggests that maturation of the gut microbiota is associated with immune and metabolic development to resist pathogen attack and prevent abnormal immune responses [2, 3]. In this critical phase, the colonization of the gut microbiota is influenced by genetic and environmental factors [4–6], including antibiotic and probiotic use.

Studies have shown that unreasonable antibiotic exposure in early life may have severe consequences for human health, which can impair immune system function, resulting in allergic asthma, gut microbiota disorder, infections, and a vicious cycle of further antibiotic use [7–11]. For maternal and infant health, antibiotic exposure in the prenatal and postnatal periods can disrupt the delicate ecosystem of the newborn microbiome and thus increase the risk of poor health outcomes [6]. Specifically, these health consequences include gut microbiota disorder of an increased microbial abundance up to 3 months after birth [12], a higher risk of obesity among 2-year-olds [13, 14], a higher risk of asthma before 5 years of age [15, 16], and a suboptimal BMI trajectory during early life [17]. However, the dose, timing, and duration of antibiotic exposure and its impact on the health of infants and young children have not been fully studied, especially based on a pregnancy and birth cohort. In underdeveloped districts, misuse and/or overuse of antibiotics during early life is a serious problem in current health practice [18–20], which may result in adverse developmental outcomes and a faster increase in antibiotic resistance. A cross-sectional study in China reported that during 2014–2018, the number of antibiotic prescriptions for pregnant women in western China was 2.1% [21], whereas during recent years, the rate may have increased under COVID-19 restrictions due to self-medication or online buying [22]. In China, antibiotic resistance genes (ARGs) have been detected in newborn faeces [23, 24]. Thus, a well-designed and constructed birth cohort is needed to further clarify the relationship between antibiotics and gut microbiota alterations from an epidemiological perspective.

Probiotics are commonly used in paediatrics and even within families to regulate gut function. Probiotics are commonly defined as “live microorganisms which, when administered in adequate amounts, confer a health benefit to the host” [25]. The Food and Agriculture Organization/World Health Organization (FAO/WHO) consultation indicated that the potential health benefit is dose-based, however, the “adequate amount” in the definition is required to assess human interventions especially in early life periods. Although encouraging, existing conclusions are preliminary without longitudinal verification, and the reasoning behind using probiotics to deal with antibiotic resistance needs more evidence [26, 27].

Improper use of antibiotics and/or probiotics contributes to the development of antibiotic resistance. The strong influence of the infant resistome is mainly through the gut, oral cavity, vagina, and breastmilk, which enrich ARGs [28]. Additionally, some probiotic strains already have natural or mutant antibiotic resistance, and consumption may help restore gut microbiota imbalance caused by antibiotic treatment; however, some specific ARGs can be transmitted vertically, e.g., maternal microbial reservoir transmission during the vaginal delivery period to the infants. Moreover, strains could transfer antibiotic resistance to pathogenic microorganisms and other gastrointestinal commensal microorganisms through horizontal transmission [29]. Combining probiotics with antibiotics can reduce the incidence and severity of antibiotic-associated diarrhoea (AAD), so some special probiotics that do not carry resistance genes are selected to treat or prevent antibiotic side-effects [30]. However, the influence of vertically and horizontally transmitted aberrant microbiota on infants needs more evidence.

To address these issues, the Pregnancy and Birth Cohort in Northwest China (PBCC) was established to (a) clarify the association among antibiotic and probiotic exposure in early life, the microecology of the gut microbiota, and the development of antibiotic resistance; (b) investigate the long-term impact of antibiotics and probiotics on the health outcomes (including birth outcome, physical and cognitive development, disease and immune response) of infants and young children; and (c) provide a theoretical basis for the rational use of antibiotics and probiotics from a life course perspective.

## Methods/design

### Study design

The PBCC is a prospective, ongoing pregnancy and birth cohort study conducted in rural, suburban, and urban areas, which are representative of the different economic levels, geographic coverage, and medical services in Shaanxi Province, Northwest China from January 2018 to December 2024. The rural site is the People’s Hospital in Binzhou city, as well as six town health centres of primary health facilities. The suburban site is Lintong District Maternal and Child Hospital, Xi’an city, which serves a mixed urban and rural population, and the urban site is the Second Affiliated Hospital of Xi’an Jiaotong University. Specifically, the birth numbers at the three sites varied, and the average numbers per year are 1731, 2040, and 3000 at the rural, suburban, and urban sites, respectively. Almost all pregnant women will deliver in hospitals, while some may deliver at home in rural areas (average of 2 per year). The caesarean rate in the three site hospitals varies between 25 and 50%, and the average rate of NICU admission is 10% but varies with hospital level. Critically ill pregnant women will be transferred to higher-level hospitals in advance. After delivery, the exclusive breastfeeding rates declined from 58.3% among newborns to 29.1% at three or four months and declined further to 13.6% among those aged five to six months [31], and the exclusive breastfeeding rates in rural areas, small urban areas and megacities at 6 months were 28.3%, 23.3%, and 35.6%, respectively. After weaning, infants usually receive formula. Child health care centres are usually located in the family’s district within a 1-h walk, and the proportion of children receiving health care is 50%-70%, but this proportion is lower in rural areas because a greater proportion of parents work outside the town.

### Sample size calculation

From the perspective of antibiotic and probiotic use in early life, we considered using probiotics to prevent antibiotic-associated diarrhoea (AAD) in infants to calculate the sample size. The rate of AAD after broad-spectrum antibiotic treatment is reported to be 25%-53% in children [32]. A meta-analysis of probiotic uses to prevent AAD and *Clostridium difficile* infection among hospitalized patients revealed a statistically significant reduction in the risks of AAD (RR = 0.61, 95% CI 0.47 to 0.79) and a lower number of CDI at the end (RR = 0.37, 95% CI 0.22 to 0.61) [33].

Therefore, with a statistical power of 90% (β = 0.1) and a two-tailed significance level of 5% (α = 0.05), for each district, the sample size was calculated using the following formula:$$n=\frac{{{(z}_{\alpha }\sqrt{2\overline{p }\overline{q}}\pm {z }_{\beta }\sqrt{{p}_{0}{q}_{0}+{p}_{1}{q}_{1}})}^{2}}{{({p}_{1}-{p}_{0})}^{2}}$$$$p_1=RR\;\cdot\;p_0$$$$\overline{p }=\frac{1}{2}({p}_{0}+{p}_{1})$$

*where p*_*0*_ denotes the risk of AAD in the control group, *p*_*1*_ denotes the risk of AAD in the treatment group, and $$\overline{q }$$=1-$$\overline{p }$$.

Then, we estimated 354 as the minimum number of participants for each group (AAD or no AAD). Considering a 15% foetus attrition rate and 5% loss to follow-up rate, we expanded the number by 20%. Hence, for the three districts, we need to enrol 2,550 participants. Finally, after discussion with the site managers, 3,000 eligible women and their healthy, singleton infants will be recruited for this study.

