#### Outcomes of interest: Birth outcomes and early health outcomes

Birth outcomes include gestational age at delivery (weeks), mode of delivery (vaginal delivery or C-section), gender, infant Apgar scores, infant anthropometric measurements, and medications. The adverse birth outcomes are as follows [37]:A low Apgar score is defined as an Apgar score at 5 min of < 7.Low birth weight is defined as a live birth weighing < 2500 g.Small for gestational age infant (SGA) is defined as birthweight < 10% of that for a specific gestational age.Preterm birth is defined as a neonate born before 37 completed weeks.

The secondary health outcomes include antibiotic resistance, disease and treatments, physical development, and cognitive development, and they are recorded at every timepoint.Antibiotic resistance: It is reported that antibiotic resistance genes were found in infant faecal samples regardless of antibiotic exposure. In the study, we use 16S rRNA microbiome high-throughput sequencing and qPCR of ARGs for antibiotic resistance gene analysis.Disease and treatment: Common diseases in children often occur in the respiratory, digestive, or urinary systems, and the medical treatment and drug history are extracted from the HIS in the hospital.Physical development: Anthropometric measurements including weight (kg), height (cm), head circumference (cm), chest circumference (cm), and mid-upper arm circumference (cm), are standardized using WHO norms [37, 38].Cognitive development is assessed by standard Bayley Scales of Infant and Toddler Development (Bayley-IV), which is a widely used, comprehensive assessment of development for infants and toddlers aged 1 to 42 months [39] administered by trained research assistants.

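### The sample size mislabels its two groups and has no factor for antibiotic or probiotic use, so the stated 90% power per district is unsupported

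*Protocol article*

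**What the plan says.** The Sample size calculation section of the protocol article bases the size on probiotics preventing AAD. The background risk is given as "The rate of AAD after broad-spectrum antibiotic treatment is reported to be 25%-53% in children", and the effect is taken from a meta-analysis that found a "reduction in the risks of AAD (RR = 0.61, 95% CI 0.47 to 0.79"). The calculation is made for each district, "with a statistical power of 90"% and at a "two-tailed significance level of 5"%. In the formula, p0 "denotes the risk of AAD in the control group" and p1 is the same risk in the treatment group, with p1 = RR x p0. The result is then reported as "Then, we estimated 354 as the minimum number of participants for each group (AAD or no AAD"). The figure is raised by 20% for foetal attrition and loss to follow-up, which gives 2,550 over three districts. The final target of 3,000 was set after discussion with the site managers.

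Elsewhere, the Participant enrolment and selection criteria admit pregnant women with no condition on antibiotic or probiotic exposure. The section on independent variables records both exposures as they occur, and the statistical analysis section uses both as comparison factors. In the outcomes section, "The secondary health outcomes include antibiotic resistance, disease and treatments, physical development, and cognitive development". Digestive-system disease falls under the disease and treatment item, but AAD is not named.

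**The concern.** There are two faults. First, AAD and no AAD are outcome groups, while the formula compares two exposure groups on that outcome, so the label contradicts the definitions just above it. Second, p0 is a risk among children who have received broad-spectrum antibiotics. The 354 per group are therefore antibiotic-treated infants, half with and half without probiotics. The step to enrolled women allows only for attrition and loss. It treats every retained infant as antibiotic-treated and evenly split by probiotic use, in a cohort where neither exposure is assigned or required.

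This is the only justification of size in the article, and it claims 90% power in each district. If the exposure shares are lower or uneven, the comparison that justified the size has less power than readers are told, and they cannot work out how much less.

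**Working it through.** **Reproducing the plan's figure.** Inputs from the Sample size calculation section: RR = 0.61, two-sided 5% (z = 1.960), 90% power (z = 1.2816). The article does not say which p0 in its 25%-53% range it used; 0.25 is the value that returns 354.

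- p1 = 0.61 x 0.25 = 0.1525; mean risk = 0.20125; difference = 0.0975.
- First term: 1.960 x √(2 x 0.20125 x 0.79875) = 1.1113.
- Second term: 1.2816 x √(0.25 x 0.75 + 0.1525 x 0.8475) = 0.7213.
- n = (1.1113 + 0.7213)² / 0.0975² = 353.3, rounded up to 354.
- 354 x 1.2 = 424.8, rounded up to 425; 425 x 2 x 3 = 2,550.

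Both figures reproduce, so the arithmetic is sound. The groups it describes are antibiotic-treated infants with and without probiotics, in a 1:1 ratio.

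**What 3,000 provides per district.** Assuming 1,000 enrolled in each district, the stated losses leave 1,000 x 0.80 = 800 if added, or 1,000 x 0.85 x 0.95 = 807.5 if applied in turn. Two groups of 354 make 708, and 708/800 = 88.5% or 708/807.5 = 87.7%. About 88% of retained infants must be antibiotic-treated, and those must split evenly by probiotic use.

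**Power under other exposure shares.** f and g are assumed, because the article gives neither. With n1 = 807 x f x g and n0 = 807 x f x (1 - g):

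power = Φ{ [(p0 - p1) - 1.960 √(p̄q̄(1/n0 + 1/n1))] / √(p0q0/n0 + p1q1/n1) }, where p̄ is weighted by group size.

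Example, f=70%, g=30%, p0=0.25: n1 = 170, n0 = 396, p̄ = 0.2207. The null standard error is 0.0380 and the alternative standard error 0.0351. Then (0.0975 - 0.0745)/0.0351 = 0.65, and power is 74%.

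The same formula, per district, at the bottom, midpoint and top of the article's risk range:

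| Assumed f, g | with v without probiotics | p0=0.25 | p0=0.39 | p0=0.53 |
|---|---|---|---|---|
| 70%, 30% | 170 v 396 | 74% | 95% | >99% |
| 50%, 30% | 121 v 283 | 59% | 85% | 97% |
| 30%, 20% | 48 v 194 | 28% | 50% | 74% |

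Using 800 in place of 807 moves these by about a percentage point at most.

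Pooled over the three districts at p0=0.25, power is >99%, 97% and 72-73% for the three rows.

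**Effect of p0 on the threshold.** The article's formula gives 194 per group at p0=0.39 and 119 at p0=0.53. With an even split, these need 388/807 = 48% and 238/807 = about 29-30% of retained infants antibiotic-treated.

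**The case against.** The best reply is that a shortfall cannot be demonstrated. The article states no infant antibiotic or probiotic rate, so every f and g above is an assumption. It also used the lowest p0 in its range, which is the conservative choice. At p0=0.39 or 0.53 several scenarios reach or exceed 90% per district, and pooled power is high in two of the three scenarios even at p0=0.25. This stands, and it is why the result is a range and the claim is called unsupported. It does not rescue the calculation, because a conservative p0 is no substitute for the missing exposure factors.

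Some stronger readings are tempting, but the article does not support them:

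- A reader might infer that the study certainly lacks 90% power. That would need known values of f and g. The figure of "the number of antibiotic prescriptions for pregnant women in western China was 2.1"% in the Background concerns maternal prescriptions, which the text says may since have risen, and cannot serve as an infant rate.
- A reader might infer that a null district result will be misread. The statistical analysis section plans no district-level AAD test; districts enter only through the size calculation.
- A reader might infer that AAD lies outside the study's outcomes. Digestive disease, with treatment and drug history, is listed, so AAD could be derived from it. It is simply not named.
- A reader might take the bracket literally, as a requirement for 354 AAD cases. The definitions of p0 and p1 show that it is a labelling slip.

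**Conclusion.** The point holds as a mislabelled pair of groups and an unstated exposure assumption, not as an arithmetic error. The 90% power per district rests on about 88% of retained infants being antibiotic-treated and evenly divided by probiotic use, at p0=0.25. Nothing in the article supports that, and its own design expects unexposed children. Over the assumed exposure shares, power per district runs from 28% to 74% at p0=0.25 and from 74% to >99% at p0=0.53.

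These figures assume an equal split of enrolment over districts, the stated losses, RR = 0.61 and no adjustment for confounding. The article should be corrected on this point. The target of 3,000 need not change, since the pooled comparison keeps useful power in most of these scenarios.

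**What to change.** In the Sample size calculation section:

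1. Relabel the two groups as antibiotic-treated infants with and without probiotic use.
2. Replace the claim of 90% power per district by the power, or the detectable RR, for the site-adjusted comparison pooled over districts. Show it over a grid of p0, f and g, using the fractions already observed in the ongoing cohort. Keep 3,000.
3. Name AAD as an outcome under disease and treatment, or base the power statement on an outcome already named.

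The cost is rewording and recalculation, with no extra enrolment. The downside is that the stated power becomes less favourable and district-level comparisons become exploratory.

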#### After birth (follow-up)

During the afterbirth period, the follow-up time points are 42 days, 3 months, 6 months, 12 months, 18 months, and 24 months of age (T5-T10 in Fig. 1). The follow-up is designed to be embedded in the scheduled immunization and child health services, and therefore the data can be collected regularly in a timely manner. Specifically, the medication and prescription drug data will be obtained by the HIS, and the face-to-face questionnaire is used to collect information on caregivers, feeding patterns, nutritional supplements, and medical and drug history, especially antibiotic and probiotic use.

We also measure the physical development of children at every follow-up time point. We use uniform measurement tools including infant scales, electronic scales, and tape measures. After calibration, weight, height, head circumference, chest circumference, and mid-upper arm circumference are measured at least twice until reaching the minimum standard, and the average is recorded. Furthermore, offspring cognitive and behavioural health will be assessed by Bayley Scales of Infant and Toddler Development (Bayley-IV) at 12 and 24 months of age, which will be conducted by trained research assistants. Likewise, questionnaires on antibiotic knowledge and caregiver behaviours will be collected at these two time points.

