## Discussion

### Strengths and limitations of this study

There are several strengths in our study. First, the study is conducted in underdeveloped districts containing rural, suburban, and urban areas in Northwest China, which could be representative and provide evidence for a similar study in other less-developed districts worldwide. Second, not only exposure data during pregnancy, but also delivery and early life data of health outcomes are collected. Third, to ensure a high follow-up response rate, a detailed investigation plan had been formulated. Furthermore, for antibiotic and probiotic assessment, a questionnaire of knowledge and behaviour related to antibiotics for parents is conducted, and the Bayley Scales of Infant and Toddler Development (Bayley-IV) are used, to make the evaluation of the results more multidimensional. However, the study has some limitations. The registration of the study is relatively late due to the COVID-19 pandemic, but the normality of the cohort is not affected by late registrations. A possible selection bias exists in the study population because investigators recruited individuals who cooperated rather than a random sample, and the rate of antibiotic use varies during pregnancy, so a large sample size is needed. Moreover, due to limitations in medical knowledge and women’s migration for work, many participants will fail to complete the follow-up of the two-year study. However, we will keep close contact with the participants to limit loss to follow-up. In addition to the time points aligned with scheduled immunization and health services, it seems urgent that we combine the information with health service systems of different institutions for the integrity of the data. In the future, if the study budget and time permit, the follow-up time will be extended.

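### The calculated enrolment of 2,550 does not restore the losses it allows for (it should be 2,631 to 2,655), and the 5% loss-to-follow-up allowance conflicts with the article's own expectation of non-completion; the planned 3,000 still covers the stated losses

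*Protocol article*

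**What the plan says.** The protocol article, under Sample size calculation, plans for "a statistical power of 90% (β = 0.1) and a two-tailed significance level of 5% (α = 0.05"), separately for each district. Its inputs are a control risk ("The rate of AAD after broad-spectrum antibiotic treatment is reported to be 25%-53% in children") and a meta-analytic "reduction in the risks of AAD (RR = 0.61, 95% CI 0.47 to 0.79"). It obtains 354 per group.

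The attrition step is: "Considering a 15% foetus attrition rate and 5% loss to follow-up rate, we expanded the number by 20" per cent. The result is: "Hence, for the three districts, we need to enrol 2,550 participants". Recruitment is then set at 3,000 after talks with the site managers. The article does not say what loss that margin is meant to cover.

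Under Strengths and limitations, the article cites limited medical knowledge and migration for work and concludes that "many participants will fail to complete the follow-up of the two-year study". It adds that close contact will be kept to limit this.

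**The concern.** There are two separate problems.

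- **Inflation.** Raising a number by 20% does not offset a 20% loss. It offsets a loss of 1 − 1/1.2 = 16.7%. The figure presented as the required enrolment therefore misses the plan's own minimum under the plan's own losses.
- **Allowance.** A 5% loss over two years is hard to square with an expectation that many will not finish. No source or reason is given for the 5%, so a reader cannot tell which statement guided planning.

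At stake are the stated requirement, and whether the reader knows how much loss the 3,000 can absorb before the claimed 90% power per district is gone.

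**Working it through.** **Inputs** (all from Sample size calculation)

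- Two-sided α = 0.05, power 90%.
- RR = 0.61.
- p0 between 0.25 and 0.53. The value used is not stated, but 0.25 reproduces the plan's figure, so p1 = 0.61 × 0.25 = 0.1525.
- Losses of 15% (foetal) and 5% (follow-up).

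**Step 1: reproduce 354.** The mean risk is 0.20125.

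n = [1.960 × √(2 × 0.20125 × 0.79875) + 1.2816 × √(0.25 × 0.75 + 0.1525 × 0.8475)]² / 0.0975² = 353.3, rounded up to 354. This matches.

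**Step 2: reproduce 2,550.** 354 × 1.2 = 424.8, rounded up to 425. Then 425 × 2 groups × 3 districts = 2,550. This matches, so the inflation was a multiplication by 1.2.

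**Step 3: apply the stated losses to 2,550.** Power = Φ{[0.0975 × √n − 1.960 × √(2 × 0.20125 × 0.79875)] / √(0.25 × 0.75 + 0.1525 × 0.8475)}.

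- Additive: 2,550 × 0.80 / 6 = 340 per group, power 88.9%.
- Sequential: 2,550 × 0.85 × 0.95 / 6 = 343 per group, power 89.2%.

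**Step 4: correct the inflation.** Completers needed: 354 × 6 = 2,124.

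- Additive: 2,124 / 0.80 = 2,655, which is 105 more than 2,550.
- Sequential: 2,124 / (0.85 × 0.95) = 2,630.3, rounded up to 2,631, which is 81 more.

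**Step 5: check 3,000 at the stated losses.**

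- Additive: 3,000 × 0.80 / 6 = 400 per group, power 93.2%.
- Sequential: 3,000 × 0.8075 / 6 = 403.75 per group, power 93.4%.

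**Step 6: the loss that 3,000 tolerates.** Total: 1 − 2,124/3,000 = 29.2%. After 15% foetal loss: 1 − 2,124/(3,000 × 0.85) = 16.7%.

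With 3,000 enrolled and 15% foetal loss, the power per district is as follows. Only the 5% row is a rate that the article states. The 16.7% row is the break-even, and the others are assumptions.

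| Postnatal loss | n per group | Power |
|---|---|---|
| 5% | 403.75 | 93.4% |
| 10% | 382.5 | 92.1% |
| 15% | 361.25 | 90.6% |
| 16.7% | 354 | 90.1% |
| 20% | 340 | 88.9% |
| 30% | 297.5 | 84.5% |

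**The case against.** The strongest reply is that the slip changes nothing in the conduct of the study. The corrected 2,631 to 2,655 lies below the 3,000 being recruited, and the error at 2,550 is worth about one percentage point of power. That stands, and it limits the point to a wrong stated figure.

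A reader might go further and infer that 3,000 fails to hold 90% power at the attrition the article describes. The route would be the Study design section, where "the proportion of children receiving health care is 50%-70%, but this proportion is lower in rural areas", joined to the follow-up section: "The follow-up is designed to be embedded in the scheduled immunization and child health services". Reading that uptake as retention would mean 30% to 50% postnatal loss and 84.5% down to 70.9% power. The article does not support this reading, for four reasons:

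- The 50% to 70% describes use of child health care in the area, not retention in this cohort.
- Follow-up also rests on immunization contacts, for which no uptake is given.
- Women must agree to two years of follow-up and those planning to move are excluded. Reminders, calls and home visits are planned.
- The word "many" is not a rate. A child who misses the last visits may still contribute to an antibiotic-associated diarrhoea comparison that the article does not tie to 24 months.

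The only attrition rates stated are 15% and 5%, and at those 3,000 suffices.

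It is also fair to say that the 16.7% tolerance is only as good as the model behind it. The article states neither a 50:50 exposure split nor 1,000 women per district, and the control risk applies after broad-spectrum antibiotics, not to every child. The tolerance should therefore be given with those conditions.

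How missing outcomes will be analysed is commonly left to the analysis plan and is not criticised here.

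What the reply does not remove is the tension between 5% and the limitations section. Planned retention efforts are a reason to hope for low loss, but they do not justify the figure.

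**Conclusion.** The point holds in two parts. First, 2,550 is too low by 81 to 105 participants (3% to 4%). At the plan's own losses it delivers 340 to 343 per group and about 89% power per district. Second, the 5% allowance is unsupported and conflicts with the limitations section. The target of 3,000 is adequate at the stated losses, with about 93% power.

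Whether 90% is kept in practice depends on postnatal loss staying at or below about 16.7%, a rate on which the article is silent. These figures rest on 0.25 versus 0.1525, equal groups, equal districts, 15% foetal loss, and every enrolled child counted in the comparison. No claim that 3,000 is underpowered follows from the article.

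**What to change.** 1. Replace 2,550 by 2,655 (losses added) or 2,631 (losses in sequence), and say which convention is used. Note that 3,000 exceeds it.
2. Reconcile the 5% with the limitations section. Either justify it or replace it, preferably with retention observed since enrolment began in 2018, if available.
3. State that, under the assumptions listed in the verdict, 3,000 keeps 90% power per district up to about 16.7% postnatal loss. Show higher losses as labelled assumptions, for example 88.9% power at 20% and 84.5% at 30%.

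The cost is a few sentences and a slightly less favourable stated figure. No extra enrolment is needed.
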